#### Other management at the discretion of the attending physician

The implementation of 80% versus 30% inspired oxygen concentration will not require alteration to usual care pathways (including use of any medication) and these will continue for both trial arms. Furthermore, there will be no anticipated harm and compensation for trial participation. There will be no restriction in the postoperative care regarding medications and therapies. All patients will be treated after completion of the study according to standard clinical care.

All aspects of the patient’s management are at the discretion of the attending physician. This includes all decisions of the intraoperatively used oxygen concentration.

Blinded research personnel will follow patients throughout their time in hospital evaluating the patients and reviewing their medical records ensuring that trial orders are followed and noting any outcomes. If patients indicate that they have experienced any of the outcome measures, the study personnel will obtain the appropriate documentation.

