## Methods/design: data collection, management and analysis

### Objectives and design

We will conduct a single-center, double-blinded, two-arm trial at the Medical University of Vienna. In total, we will randomly assign 260 patients to receive 80% versus 30% inspired oxygen concentration for surgery and for 2 h postoperatively. We will follow the Standard Protocol Items: Recommendations for Interventional Trials (SPIRIT) recommendations for interventional trials (Additional file 1). The study was approved by the Ethics Committee of the Medical University of Vienna on 13 November 2017. This trial was registered at ClinicalTrials.gov on 8 December 2017 (NCT03388957) and at the European Clinical Trial Database (2017–003714-68).

This trial will test the primary hypothesis that supplemental oxygen significantly decreases the maximal postoperative NT-proBNP concentration (assessed within 2 h after surgery, on POD 1 and POD 3) in patients with increased cardiovascular risk factors undergoing moderate- to high-risk abdominal surgery.

Our secondary outcomes are differences in maximum TnT concentration, static oxidation-reduction potential (sORP) and oxidation-reduction potential capacity (cORP), as well as vWF values and the perioperative fluid requirements to reach hemodynamic stability (Table 1).

**Table 1 Tab1:** Outcomes assessment

	Outcomes	Measurements
Primary	Myocardial function	maxNT-proBNP
Secondary	MINS	maxTnT
	Surgical stress	Copeptin
	Redox stress	sORP, cORP
	Hemodynamic	
Exploratory	Cardiac failure	50% increase in NT-proBNP
	Myocardial infarction	ECG change and elevated heart-specific enzymes
	Heart failure requiring intervention	50% NT-proBNP increase and medical treatment
	New onset of cardiac arrhythmias	ECG changes requiring medical treatment and/or electric cardioversion
	Unplanned ICU admission	

c*ORP* oxidation-reduction capacity, *ECG* electrocardiogram, *ICU* intensive care unit, *maxNT-proBNP* maximal *N*-terminal pro-B-type natriuretic peptide, *maxTnT* maximal troponin T, *MINS* Myocardial Injury after Noncardiac Surgery, *sORP* static oxidation-reduction potential

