### Intervention

After endotracheal intubation we will set the inspired oxygen fraction according to randomization. Patients randomly assigned to the 80% oxygen group will receive an inspired oxygen fraction of 0.8 after intubation; those randomly assigned to the 30% oxygen will receive an inspired oxygen fraction of 0.3 in air. Patients will be blinded to group allocation.

We will use 80% versus 30% oxygen concentration to receive the maximum difference between oxygen concentrations without the risk of causing damage, e.g., increased formation of atelectasis [19]. Moreover, almost all studies investigating the effect of supplemental oxygen on, for example, postoperative wound infection used 80% versus 30% inspired oxygen concentration during surgery [5, 6, 20].

Maintaining a minimum SpO_2_ of at least 93% will be attempted. In the case of SpO_2_ < 93% the following interventions to improve oxygenation will be performed: (1) positive end-expiratory pressure (PEEP) will be increased incrementally by 2 cmH_2_O up to maximally 12 cmH_2_O; (2) recruitment maneuver: the inspiratory pressure will be set at 55 cmH_2_O. The PEEP will be set at 12 cmH_2_O and respiratory rate to six breaths/min or higher. Inspiratory pressure will be set to receive a tidal volume of 6 mL/kg ideal BW. The inspiratory ratio will be set (I:E) to 1:1. Inspiratory pressure will be increased until a plateau pressure reaches 40–50 cmH_2_O. After allowing three breaths while maintaining a plateau pressure of 40–50 cmH_2_O, the respiratory rate and inspiratory pressure will be set back to pre-recruitment parameters and (3) if both interventions are not sufficient to increase SpO_2_, then the inspiratory oxygen fraction will be elevated by 0.1 until 93% SpO_2_ is reached.

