### Assignment to intervention

Given an average estimated recruitment rate of 10 patients per month, we anticipate a recruitment period of 25 months. A trained study coordinator will evaluate eligibility and obtain informed consent. All patients will be recruited using the operation schedule the day before surgery. After meeting the eligibility criteria, the inclusion criteria will be checked. Two copies of the signed consent form will be made. One copy remains in the patient chart, and the second one will be given to the patient. On the consent form, participants will be asked if they agree to the use of their data should they choose to withdraw from the trial. Participants will also be asked for permission for the research team to share relevant data with people from the Universities taking part in the research or from regulatory authorities, where relevant. This trial does not involve collecting biological specimens for storage.

On the day of surgery the coordinator will enroll the participants via accessing the web-based system. We will use permutated block randomization using a web-based randomization program (Randomizer, Medical University of Graz, Graz, Austria). Each block has a size of 6 numbers, randomly ordered to the two treatment assignments, of which all investigators were unaware. The web-based randomization program was set up by an investigator not involved in data acquisition. Intraoperative investigators and clinicians will be not blinded to the allocated treatment group. However, an observer strictly blinded to the group assignment will evaluate complications during hospitalization. Subsequently, a blinded investigator will call all patients 30 days after surgery and to evaluate outcomes.

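### Two sections give conflicting rules on who may change the randomised oxygen fraction: one fixes it by allocation with a single stepwise exception, the other leaves it wholly to the unblinded attending physician

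*Protocol article*

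**What the plan says.** Three sections of the protocol article bear on this.

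- **Intervention.** The allocation determines the oxygen fraction: "After endotracheal intubation we will set the inspired oxygen fraction according to randomization". The two values are 0.8 and 0.3. One route away from them is described. If SpO2 falls below 93%, PEEP is raised, then a recruitment maneuver is done, and only "if both interventions are not sufficient to increase" saturation is the oxygen fraction raised, in steps of 0.1.
- **Other management at the discretion of the attending physician.** The rule here is general: "All aspects of the patient’s management are at the discretion of the attending physician". The next sentence names the experimental variable: "This includes all decisions of the intraoperatively used oxygen concentration". It does not mention the allocation, the saturation threshold or the stepwise sequence. The same section has blinded research personnel follow patients in hospital, "reviewing their medical records ensuring that trial orders are followed and noting any outcomes".
- **Assignment to intervention.** "Intraoperative investigators and clinicians will be not blinded to the allocated treatment group". The observer who evaluates in-hospital complications is to be strictly blinded.

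The Data analysis section makes the primary analysis intention to treat. The Perioperative data section has FiO2, respiratory parameters and hourly blood gases recorded.

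**The concern.** The oxygen fraction is the only thing that distinguishes the arms. One section ties it to randomisation with a defined exception; another gives every decision about it to a clinician who knows the arm. The section heading speaks of other management, but its text reaches the randomised treatment itself.

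If clinicians used that latitude, for example by moving patients away from the assigned value for reasons other than the saturation trigger, the delivered difference between arms would shrink. Under intention to treat those patients stay in their assigned arm, so the estimated effect would be pulled towards zero. A null result could then mean either that oxygen does not affect NT-proBNP or that the arms did not differ enough. The sample size makes no stated allowance for this: the step from 254 to 260 patients is for drop-outs.

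A smaller question concerns blinding. The blinded staff both check that trial orders are followed and note outcomes. If that check included the oxygen order against the anaesthesia record, it would show them the arm.

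**Working it through.** **1. The two rules side by side**

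| | Intervention | Other management |
|---|---|---|
| Who or what sets the fraction | Randomisation | Attending physician |
| When it may change | SpO2 below 93%, after PEEP and recruitment | No condition stated |
| How far it may change | Steps of 0.1 until 93% is reached | No limit stated |
| Exception for the allocated value | Not needed | None |

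A change made without the saturation trigger falls outside the first rule and inside the second. The two therefore give different answers for the same event.

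**2. Reproducing the plan's sample size**

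Inputs, all from Sample size consideration: postoperative mean 482.49 ng/L, SD 538.78 ng/L, 40% reduction, power 80%, significance level 0.05 (taken as two-sided, as in Data analysis).

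- Difference: 0.40 × 482.49 = 193.0 ng/L.
- Standardised difference: 193.0 / 538.78 = 0.358.
- Normal approximation: n = 2 × (1.960 + 0.842)² / 0.358², giving 123 per arm, 246 in total.
- t-test: 123.3, so 124 per arm, 248 in total.
- t-test with Mann-Whitney efficiency: 123.3 / 0.955 = 129.1, so 130 per arm, 260 in total.

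The stated 254 lies between the last two. The sample size is not in dispute here.

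**3. What a loss of contrast would do**

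Let f be the share of the 193 ng/L difference lost through departures. The documents give no value for f; the values below are assumptions.

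Power = Φ(0.358 × (1 − f) × √(n/2) − 1.960). At n = 127 and f = 0, 0.358 × √63.5 = 2.854, and Φ(2.854 − 1.960) = 81.4%.

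| Assumed f | Noncentrality at 127 per arm | Power, 127 per arm | Power, 130 per arm | Total N for 80% power |
|---|---|---|---|---|
| 0 | 2.854 | 81.4% | 82.3% | 246 |
| 5% | 2.71 | 77.4% | 78.3% | 272 |
| 10% | 2.57 | 72.9% | 73.9% | 304 |
| 20% | 2.28 | 62.7% | 63.7% | 384 |
| 30% | 2.00 | 51.5% | 52.5% | 500 |

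To give f a physical meaning: if the effect were proportional to the difference in mean delivered oxygen fraction (a further assumption), the planned 0.8 − 0.3 = 0.50 would become 0.45, 0.40 and 0.35 at f = 10%, 20% and 30%.

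On this scale the six additional patients do not offset even a 5% loss: power at 130 per arm is 78.3%.

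**The case against.** **The discretion clause may be only a safety override.** It sits under a heading about other management, and the same section speaks of implementing 80% versus 30% without altering usual care. That reading is plausible, but the reader has to supply it. The sentence covers every decision on the intraoperative concentration and carries no safety qualifier. The contradiction in the text stands.

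**The power figures are not evidence of harm.** This is right. Any trial loses power if its effect shrinks, and nothing in the article says how often departures occurred. The calculation is also a normal approximation on raw values whose SD exceeds the mean, whereas the planned test is Mann-Whitney. The figures show sensitivity and nothing more.

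**Departures can largely be checked.** This also stands. FiO2, respiratory parameters and hourly pO2 are captured, and SpO2 is part of standard monitoring. It would be wrong to say that discretionary changes cannot be told apart from the stepwise escalation.

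**A reader might infer that the adherence check unblinded the outcome staff and biased the clinical events.** The documents do not support that as a fact. They do not define trial orders, which could mean blood sampling and follow-up visits, and they do not say that these staff open the anaesthesia record. The primary endpoint is a laboratory value. Adjudication of the trial outcomes gives death, infarction, acute heart failure, arrhythmias and unplanned ICU admission to a blinded adjudicator, whose decisions are used in the analysis. What remains is a possible effect on case-finding, since an adjudicator rules only on events that are brought forward.

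**A reader might also object to the statement** "We will conduct a single-center, double-blinded, two-arm trial at the Medical University of Vienna". Patients, follow-up assessors and the adjudicator are described as blinded, and the exception for intraoperative clinicians is disclosed. No error is claimed on the label.

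**Conclusion.** The contradiction between Intervention and Other management is real and concerns the randomised variable itself. As written, the second section permits an unblinded clinician to depart from the allocated fraction without condition. That could narrow the contrast and bias the intention-to-treat comparison towards no effect.

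The size is unknown. Under assumed losses of 10%, 20% and 30% of the effect, power at 127 per arm would fall from about 81% to 73%, 63% and 52%. These figures rest on the plan's raw-scale mean and SD, a normal approximation and loss rates that the documents do not give. It should not be inferred that contamination occurred or that the sample size was wrong.

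The blinding question is secondary and calls for clarification. Any bias would mainly touch case-finding for the exploratory events. Which clinical rule should prevail is not a matter for this review; the sections have to agree.

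**What to change.** 1. Reconcile Intervention and Other management so that a single rule governs departures from the assigned oxygen fraction, and state which rule was applied in practice.
2. Report delivered oxygen by arm: time-weighted intraoperative FiO2 and the hourly pO2, with the number of departures inside and outside the stepwise rule in Intervention.
3. State that the blinded staff's check of trial orders did not include the oxygen allocation or the FiO2 and blood gases in the anaesthesia record, or disclose that it did.

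Trial status says that recruitment was completed in December 2019, so conduct can no longer be changed and moving the adherence check to other staff would come too late. What remains is a wording change, one statement on blinding and a descriptive table. The FiO2 and blood-gas data are already part of the planned extraction under Perioperative data, so the cost is small. The main effort is classifying departures against the saturation trigger, as far as the recorded data allow.

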### Reporting of serious adverse events (SAE)

Serious adverse events are those which are fatal, life-threatening or fulfill the definition of being clinically important. Efficacy or safety outcomes will not be considered as SAEs, except if, because of the course of severity or any other feature of such events, the investigator, according to their best medical judgment, considers these events as exceptional in this medical condition. All events considered as part of the primary, secondary, or safety events should be reported on the appropriate page(s) in the CRF but not as an SAE, unless considered exceptional in this medical condition. In this trial, the following events (pulmonary failure, cardiac failure, myocardial infarction, acute heart failure, new onset of cardiac arrhythmias, unplanned ICU admission) are considered related to the underlying cardiovascular disease and are not considered as a SAE. These events will not be considered unexpected unless their course, severity or other specific features are such that the investigator, according to their best medical judgment, considers these events as exceptional in the context of the patient. Only unexpected and not previously described SAEs that are believed with a reasonable level of certainty to be associated with the trial medication need to be reported immediately (i.e., within 24 h of knowledge of the event) to the sponsor of the trial, the Medical University of Vienna. For such events, research personal will complete the SAE CRF immediately. Regulatory authorities will be informed in a timely manner according to the applicable regulations.

## Discussion

This study is designed to evaluate the effect of perioperative supplemental oxygen administration on postoperative NT-proBNP concentrations in patients with increased cardiovascular risk factors undergoing moderate- to high-risk noncardiac surgery. The physiological background of supplemental oxygen is to improve myocardial tissue oxygenation and simultaneously reduce myocardial oxygen consumption mediated by a reduction of the heart rate and cardiac output [11]. A recently published subanalysis of a large clinical trial showed a 30% reduction in the composite of myocardial injury, in hospital cardiac arrest and in mortality in patients undergoing colorectal surgery assigned to the 80% oxygen group [24]. Furthermore, elevated BNP and/or TnT concentrations in the immediate postoperative period are predictive of long-term outcome [16]. Interestingly, a subanalysis of a large outcome trial [25] showed that NT-proBNP and TnT are significantly increased in relatively healthy patients (unpublished data). It seems likely that the stress exposure due to surgery and anesthesia might restrain myocardial contractility, which will be reflected by the elevated NT-proBNP values. Despite the controversy regarding the harmful effects of supplemental oxygen during surgery there is evidence that oxygen might beneficially affect the cardiovascular system. In patients with central sleep apnea, for example, oxygen therapy attenuated the progression of chronic heart failure, which was assessed using BNP measurement [12]. Data of postoperative NT-proBNP concentrations, especially in patients with increased cardiovascular risk factors, are still lacking and are, therefore, of major interest. Thus, we are testing a possible beneficial effect of supplemental oxygen on perioperative myocardial function, which will be obtained by consecutive postoperative NT-proBNP measurements.

Since the effect of hyperoxia on oxidative stress is based mostly on weak studies with small sample sizes we also decided to evaluate the effect of supplemental oxygen on oxidation-reduction potential [26–28]. Measurements of sORP and cORP include all known and unknown oxidants; hence, the determination of sORP and cORP should provide a comprehensive overview of the actual system of oxidative stress.

We wish further to evaluate the immune-modulating effect of supplemental oxygen on endothelial-derived factors [29, 30]. Increased inflammation mediated by hyperoxia might result in elevated vWF-antigen concentrations reflecting endothelial damage.

Previous studies in healthy volunteers indicated a dose-dependent peripheral arterial vasoconstriction, consequently increasing systemic vascular resistance [31]. Thus, we hypothesize that intraoperative supplemental oxygen administration leads to vasoconstriction, which might reduce the required amount of fluid to maintain hemodynamic stability.

### Summary

We plan a randomized clinical trial in patients with increased cardiovascular risk factors undergoing moderate- to high-risk noncardiac surgery to compare the effects of intraoperative 80% inspired oxygen versus 30% inspired oxygen on postoperative maximum NT-proBNP concentrations. Since elevated postoperative NT-proBNP is a strong predictor for postoperative cardiac complications, patients may benefit if the postoperative NT-proBNP release can be reduced by the simple administration of supplemental oxygen.

### Trial status

Actual protocol version 1.4; 19 July 2017. Recruitment started 1 December 2017 and was completed in December 2019.

## Data Availability

The datasets analyzed during the current study are available from the corresponding author on reasonable request.

## Abbreviations

BNP: Brain natriuretic peptide
BW: Body weight
cORP: Oxidation-reduction potential capacity
DSMB: Data Safety Monitoring Board
FTc: Corrected flow time
MAC: Minimum alveolar concentration
MINS: Myocardial Injury after Noncardiac Surgery
NT-proBNP: *N*-terminal pro-B-type natriuretic peptide
PEEP: Positive end-expiratory pressure
pO_2_: Oxygen partial pressure
POD: Postoperative day
SAE: Serious adverse event
sORP: Static oxidation-reduction potential
TnT: Troponin T
vWF: von Willebrand factor
